### Recruitment {15}

Participants, non-institutionalized users with mild cognitive impairment, will be recruited from the Center of Phonoaudiological Attention of the University of Valparaíso (CAFUV) from Valparaiso (Chile). The recruitment of participants will be done by a clinical team consisting of a neuropsychologist, a clinical psychologist, and speech therapists, who will apply the instruments to corroborate the fulfilment of the inclusion–exclusion criteria. In addition, they will carry out the evaluations and interventions that the participants will receive once these users have expressed their willingness to participate in the study by signing informed consent (see Fig. 2).

**Fig. 2 Fig2:**
[figure not shown]
CONSORT diagram describing the flow of participants through the study

## Assignment of interventions: allocation

### Sequence generation {16a}

Individual participants will be allocated to either CCTP or TCTP at a 1:1 ratio through remote randomisation by the staff responsible for randomisation at the Biomedical Informatics Center Clinica Alemana—Universidad del Desarrollo, Chile (CIMB) (https://redcap.cibm.cl). The clinical trial will use the stratified randomisation method, with age (< 75 years and ≥ 75 years), sex (male and female), and years of schooling (≤ 12 years of education and > 12 years of education) as the stratification variables. Randomisation will be performed under the control of a blinded worker from CIMB, who is the only person allowed to manage the electronic coding of the randomisation to assign the individuals. The researchers will be blind to the group to which the participant is allocated.

### Concealment mechanism {16b}

In order to perform the allocation concealment process, the coded groups will be placed in sealed opaque envelopes, each marked with a participant’s code, and held by the staff responsible for randomisation. The envelopes will only be opened before the cognitive training session. To ensure proper blinding, participants will receive a code and will be shielded from the allocation process by independent CIMB staff responsible for randomisation. While the experimenter administering the intervention will be aware of the group allocation, those conducting cognitive and electrophysiological pre- and post-evaluations will remain blinded to participants’ group allocations.

### Implementation {16c}

The sealed envelopes will be opened and concealed again in the first cognitive training stage prior to the intervention by the staff responsible for randomisation. Then, the code will inform the cognitive training experimenter.

## Assignment of interventions: blinding

### Who will be blinded {17a}

The person responsible for generating the random assignment sequence list must be made aware of the people who recruit and evaluate the participants. This generated sequence will be blind until the interventions are assigned. The type of masking will be double-blind since both the participants and the professionals who perform the pre-post evaluation will. For technical reasons, professionals administering electric interventions are not blinded to the type of electrical stimulation (i.e. real or placebo) being applied. The statistician analysing outcome data will remain blind to treatment allocation throughout the analysis, which will be conducted with groups indicated by an anonymised code.

### Procedure for unblinding if needed {17b}

In the event of an adverse reaction by a participant in either treatment arm, unblinding may become necessary. Researchers will only be unblinded if knowledge of the treatment arm is deemed essential to the patient’s management by their clinical team. Any instances of unblinding will be documented, but we anticipate that they will not have a biasing effect on follow-up assessments.

## Data collection and management

### Plans for assessment and collection of outcomes {18a}

At baseline, trained researchers will evaluate the eligibility throughout a clinical semi-structured interview and application of the following scales:Montreal Cognitive Assessment (MOCA) Chilean Norm: Screening test to evaluate the general cognitive state and detection of mild cognitive impairment (MCI) elaborated by [49]. Assessment of cognitive functions, attention, abstraction, memory, language, visuospatial and visuoconstructive capabilities, calculation, and orientation.Technology-Activities of Daily Living Questionnaire (T-ADLQ) Chilean Norm [50]. The T-ADLQ assesses functional abilities of daily living in persons with MCI and the probable evolution to dementia. It is answered by the informant who accompanies the person with MCI/Dementia. The T-ADLQ measures self-care and personal care in the following areas: personal care, home care, employment and recreation, shopping and money management, travel and communication, and the use of technology.Geriatric Depression Scale of Yesavage (5-GDS). Chilean Norm [51]: An instrument widely used for depression screening. There is an abbreviated 5-item version, validated in 2000 for the Chilean population.Hopkins Verbal Learning Test-Revised. (HVLT-R). Chilean Norm [45]: Verbal learning test, which assesses anterograde memory using the immediate and delayed word repetition paradigm. In addition, it includes a recognition phase.INECO Frontal Screening (IFS-Ch) Chilean Norm [52]: The screening test that evaluates several executive processes. In particular, it evaluates motor programming, resistance to interference, inhibitory control, verbal working memory, spatial working memory, and abstraction/conceptualisation.

Later, trained researchers will realise pre-treatment and follow-up assessments at 8 and 20 weeks. They will assess electrophysiological measures underlying working memory (WM) processes, as well as performance measures in validated WM tasks, including the WAIS-IV Digit Retention subtest [44] and the Trail Making Test B (TMT-B) [45].

### Plans to promote participant retention and complete follow‐up {18b}

A researcher assistant will call participants to remember the on-site sessions (evaluations, intervention, and follow-up) and provide them with transportation for each session.

### Data management {19}

Data management will be provided by the Clinical Studies Center of Medicine Faculty of the Clínica Alemana-Universidad del Desarrollo. Interventions will be delivered on site by researchers and therapists at the Center of Phonoaudiological Attention of the University of Valparaiso (CAFUV) in collaboration with researchers of Social Neuroscience and Neuromodulation Laboratory (neuroCICS), Universidad del Desarrollo, Santiago, Chile. The CAFUV will include further patient identification centres (PICs) where needed and helpful. Potential PICs will need to be able to recruit a considerable number of patients (for more detail, see Sect. 15. Recruitment).

The Biomedical Informatics Center at Clinica Alemana-Universidad del Desarrollo in Chile (https://redcap.cibm.cl) will oversee randomisation, data management, and quality assurance under the supervision of the CI and quality assurance manager. The local ethical committee hosting the research will store routine clinical notes according to standard practice. The research team will enter assessment data on a secure, web-based system maintained by the Biomedical Informatics Center. Consent forms will be stored separately from data, and data will be anonymised wherever possible. Datasets generated and analysed during the trial will be stored in a non-publicly available repository at the Biomedical Informatics Center upon publication of the main study results. Anonymised data may be accessed and analysed by members of the project team and collaborating researchers. All personally identifiable data, except for consent forms, will be destroyed as soon as the study closes unless participants have consented to be contacted for future research, in which case their contact details will be kept for 5 years. Research data with personal information removed and replaced through a code will be retained for 5 years before destruction. Electronic records will be held for 5 years after the end of the study. Publications will not contain any patient-identifiable information.

### Confidentiality {27}

The trial data collected will be strictly confidential within the research team and services involved. Confidentiality will only be broken in exceptional circumstances when the researcher or therapist deems immediate risk is present to a patient or someone else, and the clinical team or other relevant professionals must be contacted. All data will be stored and processed under the local Ethical Committee guidelines. Personal data will be link-anonymised and identified by a code known only to the research team. Names and contact details will be stored in password-protected files on secure servers and kept separate from link-anonymised data.

### Plans for collection, laboratory evaluation and storage of biological specimens for genetic or molecular analysis in this trial/future use {33}

As described under 26b, there will be no biological specimens collected.

## Statistical methods

### Statistical methods for primary and secondary outcomes {20a}

Both the intention-to-treat (ITT) analysis set and the per-protocol (PP) analysis set will be utilised. The ITT set comprises all participants who have been randomised. When a participant is randomly assigned to a combining cognitive training group, they should be included in the combining cognitive training analysis. For the PP set, only participants who complied with combining cognitive training will be analyzed. The ITT analysis will be compared with the PP analysis to ascertain whether the two results are consistent.

#### Inferential analysis

Compliance with assumptions for parametric testing will be contrasted. In particular, univariate normality (i.e. Kolmogorov-Smirnoff, Shapiro–Wilk), sphericity (i.e. Mauchly’s W), and homoscedasticity of error variances (i.e. Levene test). If any of the above assumptions are violated, the corresponding non-parametric estimates will be provided. Mixed-model analyses without any ad hoc imputations will be used to handle missing data in case of participant drop-out and to conduct the efficacy analysis [53]. To assess distributional assumptions and the impact of missing random effect components on the model, several tests will be conducted. Normality assumptions will be examined using the Shapiro–Wilk test, skewness and kurtosis indices, and normality plots (Q-Q plots). Homoscedasticity will be investigated using Levene’s test and Box’s M test for equivalence of covariance matrices. The Wald statistic (or *Z*-test) will be utilised to test residual error variance estimation and the null hypothesis of homogeneity of residuals. The assumption that data is missing completely at random (MCAR) will be assessed using Little’s MCAR test, which remains robust to violations of distributional assumptions [54]. Additionally, the primary outcome will be evaluated using Bayesian hierarchical approaches employing JAGS and R software. In this approach, each individual beta per regressor will be subjected to a population distribution of beta values that follow a normal distribution [55]. The prior assumption for each population distribution of beta values will be flat (non-informative). The correct convergence of the Markov Chain Monte Carlo (MCMC) will be evaluated using the Gelman-Rubin statistic. The model fit will also be assessed using DIC (Deviance Information Criterion) and LOOIC (Leave-One-Out Information Criterion).

The effect sizes will be reported for each electrophysiological and cognitive performance measure analysis through the index η^2^p (partial eta square). The respective post hoc comparisons will use Bonferroni’s correction, and the effect size will be reported through Cohen’s index *d*. Graphs of the interaction effects will be provided if observed. In case of transgression of the sphericity assumption, the Greenhouse–Geisser correction will be made. Consequently, the respective parametric statistics will be provided (i.e. Friedman test, Connover’s post hoc tests). For all hypothesis tests, a significance level will be considered *⍺* = 0.05.

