### Methods in analysis to handle protocol non‐adherence and any statistical methods to handle missing data {20c}

The statistical analyses, including mixed models and Bayesian estimation, will be conducted without resorting to ad hoc imputations to manage missing data resulting from participant drop-out and to perform efficacy analysis. Little’s MCAR test will determine whether the missing data are completely at random, ensuring the robustness of the analyses even without data imputation.

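### The only non-parametric fallback the protocol names (Friedman with Conover) has no arm factor, so it cannot test group-by-time, and its standing beside the mixed model is not fixed

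*Protocol article*

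**What the plan says.** All of this is in the protocol article.

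- **Target of inference.** The Hypothesis section expects the pre-to-post rise in prefrontal theta to be larger under the combined programme (CCTP) than under the traditional one (TCTP). Trial design {8} describes a 2 × 3 mixed factorial meant to study the interaction of arm and time. Sample size {14} powers a mixed ANOVA interaction.
- **Trigger.** Inferential analysis lists tests of normality (Kolmogorov-Smirnov, Shapiro–Wilk), then "sphericity (i.e. Mauchly’s W), and homoscedasticity of error variances (i.e. Levene test"), and continues: "If any of the above assumptions are violated, the corresponding non-parametric estimates will be provided".
- **Efficacy model.** The next sentence says that mixed models "will be used to handle missing data in case of participant drop-out and to conduct the efficacy analysis". It attaches no condition. Section {20c} says the mixed-model and Bayesian analyses "will be conducted without resorting to ad hoc imputations to manage missing data resulting from participant drop-out". A Bayesian analysis is added: "Additionally, the primary outcome will be evaluated using Bayesian hierarchical approaches employing JAGS and R software".
- **Named fallback.** Later in the same section: "In case of transgression of the sphericity assumption, the Greenhouse–Geisser correction will be made". The sentence that follows is: "Consequently, the respective parametric statistics will be provided (i.e. Friedman test, Connover’s post hoc tests"). No other non-parametric method is named.

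**The concern.** A fallback for a failed assumption should answer the same question as the analysis it stands in for. Friedman's test asks whether the outcome differs between visits. It does not ask whether the arms differ in their change. Run on everyone, it tests for a time effect. Run within each arm, it gives two separate time tests and no contrast between them.

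This matters here because both arms receive the same twelve-session cognitive training (Intervention description {11a}) and the hypothesis itself allows for an increase under TCTP. A shared training gain is therefore plausible, and it is exactly the situation in which Friedman is significant without any effect of stimulation. Every hypothesis test is set at 0.05 and nothing says which result decides the trial, so the choice between an interaction test and a time test could be made after the data are seen.

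**Working it through.** **1. The plan's own figure.** Inputs from Sample size {14}: η² = 0.06, power 0.95, α = 0.05, two arms, two measurements. Assumed because not stated: correlation ρ = 0.5 and no sphericity correction.

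- f² = 0.06/0.94 = 0.0638, so f = 0.2526.
- λ = f² × N × m/(1 − ρ) = 0.0638 × 54 × 2/0.5 = 13.8, with 1 and 52 degrees of freedom.
- Power = 0.954 at N = 54, and 54 is the smallest even N that reaches 0.95. The stated 54 reproduces.
- The enrolled 62 matches 54 × 1.15 = 62.1.

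The trial is thus sized for an interaction test.

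**2. What Friedman tests.** Rank the k = 3 visits within each participant and let R̄ⱼ be the mean rank of visit j. The statistic is Q = [12N/(k(k+1))] Σ(R̄ⱼ − (k+1)/2)², which for k = 3 is N Σ(R̄ⱼ − 2)², referred to χ² with 2 degrees of freedom. Arm appears nowhere. If both arms rise together, Q is large. If they move equally in opposite directions, the pooled mean ranks stay near 2 and Q stays small.

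**3. Simulation.** Normal data, 27 per arm, three visits, unit variance, compound symmetry with ρ = 0.5 (assumed), 5,000 runs per scenario, α = 0.05. Shifts apply to both post-intervention visits. The comparator is the group-by-time F test on 2 and 2 × (54 − 2) = 104 degrees of freedom.

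| Shift in SD (CCTP / TCTP) | Pooled Friedman rejects | Interaction F rejects |
|---|---|---|
| 0 / 0 | 5.6% | 5.0% |
| +0.5 / +0.5 (no arm effect) | 89.7% | 4.6% |
| +0.7 / 0 | 53.5% | 74.0% |
| +0.35 / −0.35 | 4.3% | 75.7% |
| +0.5 / −0.5 | 3.5% | 97.4% |

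**4. How often the trigger fires by chance.** The article does not say how many assumption tests are run, so this is a range.

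- Three tests at 0.05, taken as independent: 1 − 0.95³ = 14.3%.
- Ten tests (Shapiro–Wilk by arm and visit, six; Levene by visit, three; Mauchly, one): 1 − 0.95¹⁰ = 40.1%. Simulation with normal, spherical, homoscedastic data and no arm or time effect gives 41.2%.
- Leaving Mauchly out, because sphericity has its own correction: 1 − 0.95² = 9.8% and 1 − 0.95⁹ = 37.0%.

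**5. The sphericity rule.** A sphericity failure leads first to Greenhouse–Geisser, which keeps the parametric ANOVA. The next sentence, joined by a word of consequence, leads to Friedman and Conover. The same violation therefore has two different answers, and the second carries the wrong label.

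**The case against.** The strongest reply is that nothing is switched. A reader might infer that any failed test moves the efficacy analysis to Friedman, but the text only says that non-parametric estimates will be provided. The very next sentence gives the efficacy analysis to mixed models unconditionally, {20c} repeats this, and the Bayesian analysis of the primary outcome does not depend on any assumption test. No section makes a Friedman result the criterion of success, and a time effect common to both arms would not satisfy the stated hypothesis. This stands: the documents do not support the claim that the primary question is replaced.

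Two further inferences fall with it. Friedman needs complete sets of visits and would discard participants with a missing one. That contradicts the mixed-model plan for drop-out (about 15% expected) only if Friedman replaces the mixed model; as a supplement it contradicts nothing. Also, Friedman is named straight after the sphericity sentence. Tying it to failures of normality or homoscedasticity is the natural reading, since no other fallback is named, but it is not stated.

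On size, the 41% needs ten tests, and the equal-and-opposite scenarios are extremes that require the control arm to worsen. They show that Friedman is blind to arm, not what to expect in this trial.

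What the reply does not remove is that the named fallback has no arm term, that its rank beside the mixed model is unstated, and that the sphericity rule gives two answers. These are things the article states, so an unseen analysis plan does not excuse them.

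**Conclusion.** The concern holds in a limited form. The protocol ties violation of any tested assumption to non-parametric results, and the only ones it names cannot test the interaction the trial was designed and sized for. It leaves open whether they replace or supplement the mixed model, and it prescribes both Greenhouse–Geisser and Friedman for one sphericity violation.

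If the fallback were read as efficacy evidence, an equal 0.5 SD training gain in both arms would look positive in about 90% of trials, where the interaction test rejects in about 5%. In the extreme case of +0.5/−0.5 SD, Friedman would reject in about 3% against 97%. These rates rest on 27 per arm, normal data and ρ = 0.5. The chance trigger rate of 14% to 41% rests on an assumed three to ten tests.

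This should be fixed, but it is not fatal, because an unconditional mixed-model efficacy analysis is already on the page and a short clarification settles the matter.

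**What to change.** Before unblinding:

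1. State that the arm-by-time contrast from the mixed model is the primary analysis whatever the assumption tests show.
2. Remove Friedman and Conover as a fallback for efficacy. If they are kept to describe change over time, say that they carry no evidence on the arm comparison, and correct the label to non-parametric.
3. Require any robust sensitivity analysis to retain arm. Examples are a transformed outcome in the same model, a rank-based comparison of change scores between arms, or permutation of arm labels within the randomisation strata. State that it supports the primary result and does not replace it.
4. Give one rule for a sphericity violation: Greenhouse–Geisser if an ANOVA is reported alongside, and nothing further.

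The cost is a few sentences in the analysis plan and a few lines of code. No new data are needed and the sample size does not change.

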### Sample size {14}

For the estimation of the minimum required sample size, we will consider the following parameters: (a) Effect size for the mixed ANOVA statistical test (2 × 2, with interaction effects), (b) Statistical power (1 − *β*) = 0.95 and (c) Significance level α = 0.05. We will use the G*Power 3 software to calculate [47]. Considering an effect size *η*^2^ = 0.06, the sample size amounts to 54 participants (n1 = 27; n2 = 27). As our study will be a two-intervention effect, we will consider an effect size somewhat smaller than those observed for comparisons between clinical populations of prefrontal theta oscillations during working memory: for example, Lenartowicz: *η*^2^ = 0.09 [38], and which coincides with the work of our team *η*^2^ ~ 0.1 [28]. The effect size we will use to calculate the sample is considered a moderate to significant effect according to Cohen’s criteria [48]. However, the initial sample size we propose in this project finds the proportion of participants who may present low adherence to the study. In this regard, we can point out that in a preliminary study with similar characteristics, a drop-out rate of about 15% was observed. Therefore, considering the drop-out percentage and the minimum sample size required to investigate an effect, the initial sample will be 62 participants (n1 = 31; n2 = 31).

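### The plan names a mixed model for efficacy but attaches repeated-measures ANOVA corrections and a Friedman fallback that do not fit it, without saying which result decides the trial

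*Protocol article*

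**What the plan says.** All references are to the Protocol article.

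- **Efficacy method.** Inferential analysis: "Mixed-model analyses without any ad hoc imputations will be used to handle missing data in case of participant drop-out and to conduct the efficacy analysis". Section {20c} repeats that mixed models and Bayesian estimation are used without ad hoc imputation.
- **Analysis set.** Section {20a}: "The ITT set comprises all participants who have been randomised". A per-protocol set is compared with it.
- **Sphericity, first rule.** Inferential analysis lists normality, sphericity by Mauchly's W, and homoscedasticity. It says that non-parametric estimates follow if any of them is violated.
- **Sphericity, second rule.** Later in the same section: "In case of transgression of the sphericity assumption, the Greenhouse–Geisser correction will be made". The next sentence says that Friedman and Conover tests will consequently be given. It calls them parametric, presumably a slip.
- **Effect size.** "The effect sizes will be reported for each electrophysiological and cognitive performance measure analysis through the index" partial eta squared; post hoc comparisons use Bonferroni's correction and Cohen's d.
- **Sample size {14}.** The calculation rests on "Effect size for the mixed ANOVA statistical test (2 × 2, with interaction effects". This is the only place where the article names ANOVA as a test.
- **Design {8} and Outcomes {12}.** The design is a 2 × 3 mixed factorial, with measurements before the intervention and at 1 and 12 weeks after it. The first hypothesis is a greater pre-to-post increase in prefrontal theta under CCTP than under TCTP.

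**The concern.** A mixed model and a repeated-measures ANOVA treat an incomplete participant differently. The mixed model uses the visits that exist and deals with unequal variances and correlations through the visit covariance. The standard ANOVA needs every visit from every participant and deals with the same problem by shrinking the degrees of freedom of its F test, which is what Greenhouse–Geisser does. That correction has no counterpart in a mixed model whose visit covariance is modelled.

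The section therefore gives the analyst a named model together with instructions that cannot be carried out on it, and a fallback triggered by assumption checks on the trial's own data. If the fallback is taken as the primary result, the outcome of a diagnostic test changes both who is analysed and which hypothesis is tested. Stating beforehand which result decides the trial removes that freedom.

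**Working it through.** **1. The rules side by side**

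| Step in the plan | Applies to the named mixed model? | Needs all visits? |
|---|---|---|
| Mixed model, no imputation | it is the model | no |
| Mauchly's W | no | yes |
| Greenhouse–Geisser | no | yes |
| Friedman / Conover | no | yes (complete blocks) |
| Partial eta squared | approximately, from the model's F and degrees of freedom | no |
| Bonferroni, Cohen's d, interaction graphs | yes | no |

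With two repeated measurements sphericity holds automatically. Mauchly's W and Greenhouse–Geisser therefore have meaning only for the three-visit analysis, which is the one that loses anyone missing a single visit.

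For violated sphericity, one sentence prescribes non-parametric estimates. The later pair of sentences prescribes a corrected F test and then Friedman. Friedman's test compares visits within participants and has no arm factor, so it cannot test whether the change differs between CCTP and TCTP.

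**2. The plan's sample size**

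Inputs: "Considering an effect size *η*^2^ = 0.06", "Statistical power (1 − *β*) = 0.95", "Significance level α = 0.05", two arms, two measurements. The within-person correlation is not stated; 0.5 is assumed.

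- f² = 0.06/0.94 = 0.0638, so f = 0.2526.
- Noncentrality = f² × N × m/(1 − ρ). At N = 54: 0.0638 × 54 × 2/0.5 = 13.79, with 1 and 52 degrees of freedom.
- Power is 0.954 at N = 54 and 0.947 at N = 52, so the stated 54 reproduces. With ρ = 0.3 the formula gives 74; with ρ = 0.7 it gives 34.
- The implied arm difference in change, d (in SD units), solves d² × N/[4 × 2(1 − ρ)] = f² × N × 2/(1 − ρ). This gives d = 4f = 1.01 SD for any ρ.

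**3. How many participants are affected**

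62 × 0.15 = 9.3, so about 9 lost and 53 complete. This is an upper figure: it applies the planning rate to a complete-case rule.

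**4. Power when loss is random**

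Assumptions (not in the article): 31 per arm, unit SD, visit correlations 0.6/0.6/0.45, all losses after the 1-week visit, test on 1-week change.

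SD of change = √(2 × (1 − 0.6)) = 0.894. Standard error with 62 = 0.894 × √(2/31) = 0.227. With 53 (27 + 26) = 0.894 × √(1/27 + 1/26) = 0.246.

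| True difference | Power, all 62 | Power, 53 completers | Trials where the two disagree |
|---|---|---|---|
| 0.6 SD | 74% | 67% | about 12% |
| 1.01 SD (plan's own) | 99% | 98% | between 1% and 2% |

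**5. If losses precede the 1-week visit**

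In an illustrative simulation (60 runs, two measurements, ρ = 0.5, 9 of 62 without a post value, random loss), the complete-case and mixed-model estimates correlated 0.98. Mean standard errors were 0.279 and 0.272. Participants with only a baseline add little to the contrast.

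**6. Bias when loss depends on response**

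Same set-up as step 4, with no true effect. Loss after the 1-week visit depends on 1-week change in CCTP only (about 23% lost in CCTP, 8% in TCTP). Two assumed strengths of dependence gave:

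- completer bias +0.18 SD, false-positive rate 11.7% (8.0% for the Greenhouse–Geisser interaction test), against 4.9% with all available data;
- completer bias +0.24 SD, false-positive rate 16.8% (11.4% for Greenhouse–Geisser), against 5.0% with all available data.

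The direction is stable; the size follows the assumed dependence.

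**The case against.** A reader might infer that the efficacy test is defined twice, once as an ANOVA and once as a mixed model, so that 15% of participants are in or out of the primary result. The article does not support that. Efficacy is assigned once, to the mixed model, and {20c} repeats it. ANOVA is named only as the sample-size basis, and sizing a mixed-model trial with an ANOVA formula is common. No sentence excludes drop-outs, and the 15% is a planning rate from a preliminary study. All of this stands.

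It is also fair to say that most of the reporting steps work with a mixed model. Partial eta squared can be approximated, so only the sphericity steps and the rank fallback fail to carry over. That the model is likelihood-based is inferred from the mention of random effect components and Wald tests.

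The simulated gaps depend on chosen conditions. The 74% against 67% contrast needs an effect of 0.6 SD, well below the plan's 1.01 SD, and all losses after the 1-week visit. If the ANOVA were the 2 × 2 pre-to-1-week version, those losses would remove nobody. The bias scenario assumes one-arm, response-dependent loss that nothing in the article predicts.

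What the objection does not remove is the text itself. It gives two different responses to one violation, neither applicable to the named model, and does not say whether the fallback replaces or accompanies the mixed-model result. An unseen analysis plan might settle this, but the contradiction is in what the article states, not in what it omits.

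**Conclusion.** The point holds as an internal inconsistency that should be corrected. The mixed model is the named efficacy analysis, but the attached sphericity and fallback rules belong to a complete-data analysis, disagree with each other, and are not ranked against the model.

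Followed on three visits, the ANOVA or Friedman route would drop up to about 9 of 62 randomised participants, contrary to the intention-to-treat set; Friedman would also leave the arm-by-visit hypothesis untested. Expected harm to power is slight: about one percentage point at the plan's effect size, under the assumed correlations and random loss after the 1-week visit. The more serious risk, a biased completers-only estimate, is conditional on loss after the 1-week visit depending on observed response differently by arm. The article neither predicts nor rules that out.

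**What to change.** In Inferential analysis {20a}, before unblinding:

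- State that a mixed model with arm, visit and arm-by-visit terms, and a modelled visit covariance (for example unstructured), on all randomised participants with available data is the single deciding efficacy analysis.
- Report the model-based arm difference in change with its 95% confidence interval.
- Remove Mauchly's W, Greenhouse–Geisser and the Friedman/Conover switch as steps of that test, or label any complete-case ANOVA or rank analysis a sensitivity analysis that does not decide the trial.
- If a sphericity rule is kept for such a sensitivity analysis, give one response to a violation, not two.
- Partial eta squared may stay as a descriptive supplement, which preserves comparison with the effect sizes cited in Sample size {14}.

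The degrees-of-freedom method can be left to the statistical analysis plan. The cost is rewording one section; no participants, visits or data are added.
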